**Figure 3 F3:**
[figure not shown]
Overview of the brief smoking cessation intervention.

#### Refer

The provider letter will describe the benefits of smoking cessation, advise the patient to quit smoking, and notify them they will receive a call from the ITQL within the next 48 h. Once the patient views the electronic provider letter via the patient portal, an automated referral will be sent to the ITQL with the patient's name, phone number, and unique ID number. Patients will also be allowed to opt-out of the treatment engagement call.

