All English-speaking adult patients at three MSHC locations (Main, South Shore, and Englewood) who smoke and are enrolled in the UI Health Patient Portal will be eligible for this pilot test. An equal number of patients (total *N* = 100) will be randomly selected from each location for the feasibility trial using a software program developed by programmers at the University of Illinois at Chicago. Human subject approval will be obtained before data collection, and formal informed consent obtained from participants.

Figure 3 displays an overview of the activities to be conducted in Aim 4 of the study. The intervention will be based on the 3 A's framework (Ask-Advise-Refer, [AAR]) (9, 11, 12). In the first phase of this aim, we will *Ask and Identity, All Smokers*. Project staff will review the electronic health record of the six participating clinic locations to identify all current smokers. Any patient without documented smoking status will be flagged for input during the subsequent clinical encounter. Next, we will *Advise a Quit Attempt*. A random selection of all smokers enrolled in the patient portal will be sent a signed letter from their provider via the portal. The letter will describe health risks associated with smoking, explain the availability of free treatments, strongly encourage the patient to make a quit attempt, and inform them that they will be receiving a call from the Illinois Tobacco Quitline. Patients will be informed that the ITQL will provide free smoking cessation counseling and nicotine replacement therapy (nicotine patches). An automated text or email message with a hyperlink to the portal login page will be generated and sent to patients to alert them of the message from their providers.

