#### Address Barriers

Quitline counselors will make 5 attempts to reach the patient before referring the case to the MiQuit Care patient navigator. Trained patient navigators will call non-responders to encourage them to make a quit attempt and engage with the tobacco quitline. A standardized assessment of the patient's interest in smoking cessation and barriers to engagement with the quitline will be conducted. Smokers who are not interested in quitting will receive brief motivational counseling and be advised to make a quit attempt soon. Smokers interested in quitting smoking will be referred to the quitline by the patient navigator using the patient portal. MSHC has an existing lung health navigation program for smoking cessation and lung cancer screening. Study investigators will oversee the training and ongoing supervision of existing lung health patient navigators to ensure fidelity to the treatment protocol.

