### Data Analysis

Consistent with RE-AIM (32), our primary outcomes will include Reach and Impact (Reach x Efficacy). We will obtain feasibility data from the patient portal. First, we will assess which patients received (opened) an electronically generated message from their providers advising them to make a quit attempt, describing free stop smoking services from the ITQL, and informing them about an upcoming call from the ITQL. All patients will be allowed to opt into the proactive ITQL counselor call. We will evaluate what percentage of patients opt-in to treatment and the demographic factors associated with the decision to accept linkage to the ITQL. Next, we will assess the percentage of patients who opted-in to treatment and were subsequently reached by the ITQL. Finally, we will evaluate the percentage of patients who engaged in stop smoking treatment (participated in more than 1 counseling call) and their quit outcomes. Patient receipt of treatment and self-reported quit rates will be obtained from the ITQL. The ITQL will provide a monthly report on patient engagement and quit rates. Statistical analyses (multivariable logistic regression models) will be conducted to determine demographic factors (age, race, gender, clinic) associated with receipt of the provider message and advice to quit smoking, receipt of treatment by the ITQL, and quit rates. One of our smoking cessation patient navigators will contact patients who opted-in to linkage to the ITQL and who were not reached by an ITQL counselor. Patient navigators will record barriers to quitline engagement that will be qualitatively analyzed. Data from this aim will refine implementation strategies and procedures in preparation for a fully powered randomized controlled trial.

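### Quitline linkage is opt-out with automatic referral in the Aim 4 procedures but opt-in in the Data Analysis, so every count from the linkage step onward depends on which rule holds

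*Protocol article*

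**What the plan says.** **Procedures (Protocol article, Study Procedures, Aim 4).** The provider letter is to "inform them that they will be receiving a call from the Illinois Tobacco Quitline". Under Refer, the trigger is viewing the letter: "Once the patient views the electronic provider letter via the patient portal, an automated referral will be sent to the ITQL". The patient's choice is then to decline: "Patients will also be allowed to opt-out of the treatment engagement call". Under Address Barriers, the quitline makes 5 attempts before handing the case over, and "Trained patient navigators will call non-responders to encourage them to make a quit attempt and engage with the tobacco quitline". No opt-in condition is attached to that step.

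**Analysis (Protocol article, Data Analysis).** Reach and Impact (Reach x Efficacy) are named as primary outcomes, followed by a chain of steps. The first is which patients opened the message. The patient's choice is then described the other way round: "All patients will be allowed to opt into the proactive ITQL counselor call". Three steps are built on that choice:

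- acceptance: "We will evaluate what percentage of patients opt-in to treatment and the demographic factors associated with the decision to accept linkage to the ITQL";
- contact: "we will assess the percentage of patients who opted-in to treatment and were subsequently reached by the ITQL";
- navigation: a patient navigator "will contact patients who opted-in to linkage to the ITQL and who were not reached by an ITQL counselor".

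The article does not describe an opt-in action in the portal, and it does not say that a patient who does not decline is to be counted as having opted in.

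**The concern.** Under automatic referral with a right to decline, the only choice that can be observed is refusal. The analysis, however, sets out to measure acceptance and to model who accepts. As both are written, the planned acceptance percentage and its predictors cannot be obtained from the planned procedure.

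The difficulty lies with the patient who opens the letter and takes no action. That patient is referred under the Refer section but has not opted in under the Data Analysis section. The acceptance percentage, its correlates, the base for the contact percentage and the navigator group all turn on how that patient is classified.

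The article says that data from this aim will refine procedures for a fully powered randomized trial. If a passive default were reported as opt-in, active acceptance of linkage would be overstated and the later trial could be planned on the wrong quantity. The rule also decides whether the patient's name and telephone number go to the quitline without an active choice. The Aim 4 protocol, still to be reviewed by the IRB according to the Ethics Statement, would need to state this consistently.

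**Working it through.** The article gives no linkage, refusal or contact rate and no power calculation for Aim 4, so there is no figure to reproduce. The check is a comparison of the two descriptions, followed by arithmetic on assumed rates.

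**Step 1. Classify each possible viewer under each rule.**

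| Viewer of the letter | Refer section (opt-out) | Data Analysis section (opt-in) |
|---|---|---|
| Actively accepts | referred | opted in |
| Takes no action | referred | not opted in |
| Declines | may opt out of the call | not opted in |

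The two descriptions differ only in the second row. The opt-in group lies inside the group that does not decline, and the two coincide only if no viewer is silent. Patients who never open the letter are outside both groups, so the letter-opened step is the same under either rule.

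**Step 2. Put numbers to the second row.** The pilot size of 100 comes from the article. The rest are assumptions: V = 60 viewers, a proportion d = 0.10 of viewers declining, and a proportion s of viewers silent, taken as 0, 0.30 or 0.60. Behaviour is held fixed and only the rule changes.

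- Linked under opt-out = V x (1 - d) = 60 x 0.90 = 54, whatever s is.
- Linked under opt-in = V x (1 - d - s):
  - s = 0: 60 x 0.90 = 54
  - s = 0.30: 60 x 0.60 = 36
  - s = 0.60: 60 x 0.30 = 18

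The ratios are 54/54 = 1.0, 54/36 = 1.5 and 54/18 = 3.0. As a share of viewers, linkage is 90% under opt-out and 90%, 60% or 30% under opt-in.

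**Step 3. Carry it to the contact step.** Assume half of those linked are reached. As a share of the 100 selected patients, the reached percentage is 0.5 x 54 = 27% under opt-out, and 27%, 18% or 9% under opt-in.

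**Step 4. Vary the number of viewers.** With 40 viewers, 36 are linked under opt-out and 36, 24 or 12 under opt-in. With 80 viewers the figures are 72, and 72, 48 or 24. The reached share over the whole grid is 18% to 36% under opt-out and 6% to 36% under opt-in. The ratios do not depend on V.

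**Step 5. Check the navigator step.** Under Address Barriers the group is everyone the quitline tried 5 times without success. Under Data Analysis it is those who opted in and were not reached. The quitline can only try patients who were referred to it, so the two groups differ because of the same silent viewers.

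**The case against.** The strongest reply is that a single default is intended, namely automatic referral with a right to decline, and that the Data Analysis section merely uses opt-in loosely. In support, that section's own description of the letter has it announcing a forthcoming call. On this reading only terms need correcting. That is plausible, but the article never equates the two, and three separate steps use the opt-in wording. Even on this reading, the analysis of a decision to accept would have to become an analysis of declining. Figure 3 is not shown. It may clarify the flow but cannot remove two conflicting sentences.

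It can also be said that this is a small feasibility pilot, that the article plans a design phase in which system rules will be documented, and that Aim 4 had not started. This stands, and it makes the repair easy. It does not tell the design team which of the two rules to build.

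Three stronger readings are tempting and are not supported:

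- A reader might infer that the primary Reach outcome itself is defined on two incompatible populations. The article gives Reach no numerator or denominator, the first step of the chain is common to both rules, and the populations are nested.
- A reader might count the navigator step as a second, independent contradiction. It largely follows from the same conflict, and the groups coincide once one linkage rule is applied.
- A reader might set a low refusal rate against a low acceptance rate, for example 5% declining (60 x 0.95 = 57) against 10% agreeing (60 x 0.10 = 6), and report a ratio of 9.5. Such rates are chosen independently and do not hold patient interest fixed, so the ratio shows nothing about the effect of the rule.

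**Conclusion.** The contradiction is explicit in the printed text and needs correcting. From the linkage step onward, the counts and denominators that feed Reach and Impact depend on whether silence means referral or non-acceptance; the letter-opened step is unaffected. With 10% of viewers declining and up to 60% silent, the number linked differs by a factor of 1.0 to 3.0. This range illustrates sensitivity to the rule and does not estimate bias: every rate in it is assumed, and the factor is 1.0 if no viewer stays silent. Overstatement of acceptance would arise only if non-refusal were reported as opt-in. The article does not announce that, but its wording allows it.

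**What to change.** Reconcile the Refer, Address Barriers and Data Analysis sections to one linkage rule before the portal application is built. Then:

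- Log these as separate dated events for each patient: letter opened, declined, actively accepted, referral sent, reached, and more than 1 counseling call.
- If referral is automatic on viewing, replace the opt-in percentage with the percentage not declining, and model declining.
- If active acceptance is required, remove the automatic referral on viewing and describe the act by which the patient accepts.
- State the denominator of each step. Percentages conditional on the previous step are legitimate in a cascade. Reporting every step over all selected patients as well would be useful but is a preference and is not needed to resolve the conflict.
- Describe the navigator group in the same terms under Address Barriers and Data Analysis.

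The cost is protocol wording and a specification for event logging. The article puts application development in the future and says Aim 4 had not started, so no data would be affected. An acceptance or refusal that the system never logged could not be recovered afterwards.

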#### Treatment

A trained tobacco quitline counselor will call patients. Once reached, quitline counselors will assess the patient's readiness to quit smoking and provide an appropriate treatment plan. If interested in making a quit attempt, quitline counselors will provide smokers with an overview of the program, obtain cessation goals, recommend a treatment approach (counseling only or counseling + nicotine replacement therapy), and schedule the next session. The ITQL counseling program is based on the Freedom from Smoking (46, 47) program. It offers up to 6 weeks of free nicotine replacement (patches) to those 18 and older, medically eligible, and uninsured or on Medicaid. The American Lung Association operates the Illinois Tobacco Quit Line. Certified counselors speak both English and Spanish and have expertise in the treatment of diverse smokers.

#### Address Barriers

Quitline counselors will make 5 attempts to reach the patient before referring the case to the MiQuit Care patient navigator. Trained patient navigators will call non-responders to encourage them to make a quit attempt and engage with the tobacco quitline. A standardized assessment of the patient's interest in smoking cessation and barriers to engagement with the quitline will be conducted. Smokers who are not interested in quitting will receive brief motivational counseling and be advised to make a quit attempt soon. Smokers interested in quitting smoking will be referred to the quitline by the patient navigator using the patient portal. MSHC has an existing lung health navigation program for smoking cessation and lung cancer screening. Study investigators will oversee the training and ongoing supervision of existing lung health patient navigators to ensure fidelity to the treatment protocol.

### Data Analysis

Consistent with RE-AIM (32), our primary outcomes will include Reach and Impact (Reach x Efficacy). We will obtain feasibility data from the patient portal. First, we will assess which patients received (opened) an electronically generated message from their providers advising them to make a quit attempt, describing free stop smoking services from the ITQL, and informing them about an upcoming call from the ITQL. All patients will be allowed to opt into the proactive ITQL counselor call. We will evaluate what percentage of patients opt-in to treatment and the demographic factors associated with the decision to accept linkage to the ITQL. Next, we will assess the percentage of patients who opted-in to treatment and were subsequently reached by the ITQL. Finally, we will evaluate the percentage of patients who engaged in stop smoking treatment (participated in more than 1 counseling call) and their quit outcomes. Patient receipt of treatment and self-reported quit rates will be obtained from the ITQL. The ITQL will provide a monthly report on patient engagement and quit rates. Statistical analyses (multivariable logistic regression models) will be conducted to determine demographic factors (age, race, gender, clinic) associated with receipt of the provider message and advice to quit smoking, receipt of treatment by the ITQL, and quit rates. One of our smoking cessation patient navigators will contact patients who opted-in to linkage to the ITQL and who were not reached by an ITQL counselor. Patient navigators will record barriers to quitline engagement that will be qualitatively analyzed. Data from this aim will refine implementation strategies and procedures in preparation for a fully powered randomized controlled trial.

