### Tobacco Cessation Treatments

In 2000, the U.S. Public Health Service clinical practice guideline, Treating Tobacco Use and Dependence, recommended that providers consistently identify and document patients' tobacco use status and treat tobacco users via the “5As” framework (Ask-Advise-Assess-Assist-Arrange) (6). Although effective, the 5As model is time-consuming and can be challenging to implement in high-volume clinical settings (7). A simplified version of the framework (Ask-Advise-Refer, [AAR]) was subsequently developed (8). When implemented in clinical settings, AAR has demonstrated effectiveness for increasing patient engagement with recommended treatment approaches such as state tobacco quitlines (9–12). State-run tobacco quitlines offer free telephone counseling and nicotine replacement for low-income smokers. The average quit rates among quitline users are 12.7%, increasing to 28.1% when counseling is combined with nicotine replacement (6). Despite the efficacy of provider interventions such as AAR for linking smokers to treatment, these interventions are underutilized in clinical settings.

FQHCs are required to report annually on their implementation and dissemination of evidence-based tobacco cessation per their Uniform Data Set (UDS) guidelines for FQHCs (5). The Centers for Disease Control and Prevention reports that, although 62.7% of outpatient visits included tobacco screening, only 20.9% of current tobacco users received counseling and 7.6% received a prescription for pharmacotherapy during their visit (13). Barriers to provider adherence to AAR practice guidelines are well-documented (i.e., time restraints) (7). As such, innovation in implementing AAR clinical practice guidelines is needed to facilitate the delivery of evidence-based smoking cessation treatments, especially in clinical populations disproportionately burdened by tobacco use.

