To date, a small number of randomized controlled trials have used the EHR to identify an entire population of smokers and proactively engage them in treatment (14, 18–21). Proactive engagement can be defined as the systematic targeting of all smokers in a population (e.g., health care system). Proactively calling smokers in the general population to offer free quitline counseling increases quit attempts and cessation rates (22). Several trials have demonstrated the benefit of population-based outreach efforts compared to standard clinical practice on receipt of smoking cessation counseling or medications (range 12.8–14.5 vs. 5.1–7.3%, respectively), and abstinence rates (range 5.3–13.5 vs. 1.1–10.9%, respectively) (20). A few studies have evaluated the reach and feasibility of delivering health promotion interventions *via* patient portals (14, 23). However, few have tested the use of patient portals to offer population-level smoking cessation treatments consistent with the AAR framework that directly links smokers to a state tobacco quitline and does not require trained clinical staff to implement.

Despite the early promise, the potential of patient portals as a health intervention delivery system will be limited by patient enrollment, especially among patients impacted by the digital divide (24). Integrating the promotion of patient portal use into routine primary care practices and offering assistance in enrollment may increase the use of patient portals (25). Patient navigation (PN) is a recognized and evidence-based approach for reducing health inequalities (26) and has been shown to increase patient access to health care services (27). The primary role of the PN is to address patients' informational, emotional, and practical needs associated with accessing health care. A recent meta-analysis of randomized clinical trials of PN interventions demonstrated that, compared to usual care, patients who received PN were significantly more likely to access health screening (OR 2.48, *p* < 0.00001) and to attend a recommended care event (OR 2.55, *p* < 0.01) (27). However, more research is needed to evaluate whether PN can increase patient portal access among patients with low health literacy, racial/ethnic minorities, and patients with limited computer skills; thereby, helping to realize the potential of patient portals for widespread delivery of smoking cessation interventions.

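### With 100 patients, the four-factor logistic models for quitline treatment and quitting have too few events to identify demographic factors

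*Protocol article*

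**What the plan says.** The Aim 4 sample is described under Study Procedures: "An equal number of patients (total *N* = 100) will be randomly selected from each location for the feasibility trial". The eligible population is "All English-speaking adult patients at three MSHC locations (Main, South Shore, and Englewood) who smoke and are enrolled in the UI Health Patient Portal", so clinic has three levels.

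The Data Analysis section then commits to one model form for three outcomes. It says "Statistical analyses (multivariable logistic regression models) will be conducted to determine demographic factors (age, race, gender, clinic) associated with receipt of the provider message", and the full list of outcomes is "receipt of the provider message and advice to quit smoking, receipt of treatment by the ITQL, and quit rates". The same section takes treatment receipt and self-reported quitting from the quitline's own reports, and it counts a patient as engaged only after more than one counselling call.

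The article states no expected number of treated patients or quitters for Aim 4. The only relevant rates are in the background section, Tobacco Cessation Treatments:

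- For population outreach against standard practice: "receipt of smoking cessation counseling or medications (range 12.8–14.5 vs. 5.1–7.3%, respectively". The same sentence gives abstinence of 5.3 to 13.5% under outreach.
- For quitline users: "The average quit rates among quitline users are 12.7%, increasing to 28.1% when counseling is combined with nicotine replacement".

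**The concern.** A logistic model draws its information from the rarer of the two outcome categories. Four covariates, one of them a three-level clinic factor, need at least five slopes. If only a few patients are treated or quit, two things can happen. Some covariate pattern may contain no events, in which case maximum likelihood has no finite estimate (separation). Or the model fits, but with odds ratios that are biased away from 1 and have very wide intervals.

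At stake is how the pilot's secondary findings are read. The plan says the models will determine which factors are associated with treatment and quitting, and that Aim 4 data will refine implementation strategies and procedures before a fully powered trial. Unstable odds ratios are a poor basis for that.

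**Working it through.** There is no sample-size calculation to reproduce, because N = 100 is stated without inputs. The check asks how many events the article's cited rates would give.

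**Slopes.** Age 1 + gender 1 + clinic 2 (three clinics) + race at least 1 = 5. With race in three groups there are 6.

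**Treated patients.** 100 × 0.128 = 12.8 and 100 × 0.145 = 14.5. Per slope: 12.8/5 = 2.6 and 14.5/5 = 2.9 (2.1 and 2.4 with six slopes).

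**Quitters, two routes.**

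- Treated, then quit: 100 × 0.128 × 0.127 = 1.6 up to 100 × 0.145 × 0.281 = 4.1. Per slope: 1.6/5 = 0.3 and 4.1/5 = 0.8.
- Abstinence under outreach applied directly: 100 × 0.053 = 5.3 up to 100 × 0.135 = 13.5. Per slope: 5.3/5 = 1.1 and 13.5/5 = 2.7.

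Together these give about 2 to 14 quitters, or 0.3 to 2.7 per slope.

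**A clinic without quitters.** Take 4 quitters and clinics of 33, 33 and 34. The chance that at least one clinic has none is [2·C(67,4) + C(66,4) − 2·C(33,4) − C(34,4)] / C(100,4) = (1,532,960 + 720,720 − 81,840 − 46,376) / 3,921,225 = 0.54. With 2 quitters over three clinics it is certain.

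**Estimability.** For each scenario, 1,000 data sets of 100 patients were simulated with no true covariate effect and checked for separation by linear programming. The article gives 74% Black patients. Assumed, and not in the article: 60% in one gender, standardised age, and the other 26% either as one race group or as two groups of 13%.

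| Outcome and rate | Expected events | Not estimable, binary race | Not estimable, three race groups |
|---|---|---|---|
| Treated, 12.8% | 12.8 | 5% | 36% |
| Treated, 14.5% | 14.5 | 4% | 30% |
| Quit, 1.6% | 1.6 | 95% | 99% |
| Quit, 4.1% | 4.1 | 67% | 90% |
| Quit, 5.3% | 5.3 | 56% | 82% |
| Quit, 13.5% | 13.5 | 4% | 33% |

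In a second simulation the number of quitters was held fixed (600 data sets per case, binary race, equal gender). Separation occurred in 100% of data sets at 2 quitters, 77% at 4 and 50% at 5.

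**Precision where the treatment model fits.** With binary race, the median standard error of the log odds ratio is 0.64 to 0.66 for gender and 0.75 to 0.79 for a clinic contrast. The 95% interval therefore runs from the estimate divided by exp(1.96 × SE) to the estimate multiplied by it: a factor of about 3.5 for gender and about 4.5 for clinic. At 13.5 quitters the quit model has much the same precision.

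**Higher uptake.** Suppose all 100 patients were treated. The cited quit rates give 12.7 to 28.1 quitters, or 12.7/5 = 2.5 to 28.1/5 = 5.6 per slope. Reaching 5 per slope (25 quitters) at the highest cited rate needs 25/0.281 = 89 of the 100 to be treated.

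**Message opening.** No opening rate is given. If half opened the message, there would be 50 events, about 8 to 10 per slope, and separation in at most 0.5% of data sets.

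**The case against.** The strongest reply is that these rates are not planning assumptions for Aim 4. They come from other programmes. Aim 4 patients are already portal users, viewing the letter triggers an automatic referral, and navigators call those the quitline cannot reach, so uptake may be higher. That stands as a limit on the counts. It does not rescue the quit model, which stays thin even if everyone is treated. The requirement of more than one call, and the losses at opening, opting in and being reached, could also push the counts down.

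The second reply is that this is a pilot whose primary outcomes are reach and impact. Percentages are already planned along the pathway, and the handling of sparse data belongs in a fuller document. Pilot status does lower the weight of the point. But the article states the method, the covariates, the outcomes and the sample size, so the mismatch lies in what is written and not in an omitted detail.

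A reader might infer more than the documents support:

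- *That both models will mostly fail to be estimable.* The treatment model usually fits; its problem is overfitting and imprecision.
- *That only two to four quitters can be expected.* The article's direct abstinence range gives 5 to 14. The lower count matches the stated data source somewhat better, because quitting is reported by the quitline, but the article does not fix either.
- *That the results are meant to select subgroups for the later trial.* Demographic targeting of outreach appears only under Aim 3, for portal enrolment.

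**Conclusion.** The point holds for two of the three modelled outcomes. On the only rates the article cites, the treatment model would have 2 to 3 events per slope: usually fittable, but too imprecise to identify factors. The quit model would have 0.3 to 2.7 per slope: not estimable in most data sets at 2 to 4 quitters and in about half at 5, with failure down to 4% (binary race) or 33% (three race groups) at 13.5. Ordinary maximum-likelihood models cannot do what the plan asks of them for these outcomes.

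This rests on background rates carried over to Aim 4, on five or six slopes, and on the assumed gender, age and race mix in the simulations. The message-opening model is not shown to be at fault. No primary outcome depends on the affected models, so this is a correction that should be made and not a flaw in the trial's main result.

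**What to change.** Change the analysis wording in Data Analysis:

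1. For treatment by the quitline and for quitting, report counts and proportions with exact 95% confidence intervals, overall and by clinic, race and gender, with the denominator stated.
2. If associations are examined for these two outcomes, use Firth-penalized or exact logistic regression with one pre-named covariate at a time, labelled exploratory. Drop the claim that the models determine factors.
3. Keep the multivariable model for message opening only if the observed numbers opened and not opened both support at least five slopes.

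The cost is the loss of adjusted odds ratios for treatment and quitting, which the expected data would not support. Sample size, procedures and data collection are unchanged.
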